### Statistical analysis

2.5

Through utilizing the software of IBM SPSS Statistics for Windows, version 20, all the data can be analyzed (IBM Corp., Armonk, NY). Afterwards, all the data are described with appropriate characteristics such as mean, median, standard deviation, as well as percentage. The qualitative parameters for the groups are evaluated by *t* test. The categorical variables are determined by the *χ*^2^ tests. When *P* is less than .05, it is viewed to be significant in statistics.

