### Inclusion and exclusion criteria

2.2

100 patients are included in the trial. In this study, patients meeting the following criteria will be included:

(1)patients aged 18 or older,(2)stage I to III disease,(3)patients newly diagnosed with the breast cancer, and(4)patients undergoing surgery accompanied by adjuvant therapy.

And patients with

(1)mental or cognitive disorders and(2)other malignancies will be excluded.

Sequence of random numbers is generated by a computer. Sequentially numbered sealed opaque envelopes are used for the concealment of random numbers. All patients participating in our experiment are randomly assigned to the study group and the control group, each group with 50 members.

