### Intervention

2.3

In intervention group, the patients are given multi-mode nursing program based on WeChat and routine nursing, the details are as follows:

(1)Physical rehabilitation:a.Offer the personalized information: adverse reactions of the adjuvant therapy; postoperative complications; complications of an implantable venous access or the peripheral insertion of central catheter.b.Self-monitoring and prevention of recurrence after discharge.c.Drawing up and then updating the patient-oriented activity, rest, and diet plans.d.Dealing with the fatigue and lack of sleep: engaging in physical activity and relaxation exercise (such as meditation, listening to music, muscle relaxation).(2)Psychological rehabilitation:a.Conducting demand-oriented psychological counseling.b.Family (face-to-face guidance by professionals): meeting the patients’ needs; understanding their feelings; and accompanying them as much as possible.c.Peers (face to face guidance by professionals): sharing relevant experiences in coping with the negative mental state.(3)Social rehabilitation: Role transformation: Gradually accomplishing the transformation of role from the patient to social role; and fulfill their original social role.

The project team based on WeChat involves 3 researchers and 1 postgraduate student majoring in breast cancer nursing, and 1 nurse and 1 doctor from the surgical department of breast cancer. All the members take part in scheme design; 2 of the members are tasked with preparing and transmitting information; 3 members are responsible for handling issues that arise on WeChat platform. The intervention duration ranges from hospitalization to 6 months postoperatively. In control group, patients are given routine nursing, involving vital signs monitoring, the education of health, the monitoring of postoperative complications, as well as postoperative drainage tube nursing.

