### Outcomes

2.4

The main outcomes is the change of Functional Assessment of Cancer Therapy-Breast version 4.0 (FACT-Bv4.0) score.^[15]^ The evaluation includes social well-being, physical health, functional well-being, and emotional well-being, as well as the “breast cancer-specific additional concerns subscale.” While the secondary result is the numerical rating scale (NRS).

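### The change in FACT-B is to be compared by a t test with no covariate; adjusting for the baseline score would generally be more precise and would remove the effect of a chance baseline imbalance.

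*Protocol article*

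**What the plan says.** The Outcomes section (2.4) defines the primary endpoint: "The main outcomes is the change of Functional Assessment of Cancer Therapy-Breast version 4.0 (FACT-Bv4.0) score". A change can only be formed if each patient has a score before and after, so a baseline FACT-B is implied, although the article prints no assessment schedule.

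The Statistical analysis section (2.5) gives two tests. The first is "The qualitative parameters for the groups are evaluated by *t* test"; the second is "The categorical variables are determined by the *χ*^2^ tests". Because categorical variables have their own test, the first sentence must concern quantitative variables, and the t test is the only listed method that fits a score. The threshold is stated as "When *P* is less than .05, it is viewed to be significant in statistics". No covariate, regression model or baseline adjustment is mentioned.

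Section 2.2 gives the size and allocation: "100 patients are included in the trial", with "each group with 50 members". It describes no stratification. Table 1 has one column per group and one P value per row, with no baseline column and no adjusted difference, which fits a plain two-group comparison.

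**The concern.** Subtracting the baseline amounts to adjusting for it with a slope fixed at 1. The true slope of follow-up on baseline is usually below 1, so the change score over-corrects. Two things follow. First, the difference between groups is estimated with more variance than the same data allow. Second, if one arm happens to start higher, its mean change is pulled down by regression to the mean, and the unadjusted comparison carries that shift.

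With 50 per arm and no stratification described, such imbalances are not rare. At stake are a wider confidence interval than necessary for the main outcome, and a result that a reader could attribute to the luck of the allocation.

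**Working it through.** **Inputs from the document.** n = 50 per arm (2 × 50 = 100, which agrees with the stated total); significance level 0.05. The article gives no effect size, SD or power, so no precision or power figure of the plan's own can be reproduced.

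**Assumptions not in the document.** Two-sided testing; t test applied to change scores; the same SD σ at baseline and follow-up; baseline to follow-up correlation ρ from 0.3 to 0.8. For the power column, a true effect of 0.5σ.

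**Precision.**
- Variance of a change score: 2(1 − ρ)σ².
- Residual variance under ANCOVA: (1 − ρ²)σ² = (1 − ρ)(1 + ρ)σ².
- Ratio, ANCOVA to change: (1 + ρ)/2.

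| ρ | Variance ratio | Power at 0.5σ, change → ANCOVA |
|---|---|---|
| 0.3 | 0.65 | 56.1% → 74.6% |
| 0.5 | 0.75 | 70.5% → 82.3% |
| 0.7 | 0.85 | 89.8% → 93.8% |
| 0.8 | 0.90 | 97.7% → 98.6% |

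The power figures use the normal approximation. A simulation of 20,000 trials at ρ = 0.5 gave 69.9% and 81.4%, with standard errors of 0.200σ and 0.173σ. The mean estimate was about 0.499σ for both methods, so neither is biased on average.

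**Detectable difference at ρ = 0.5.** The change-score SD is σ√(2 × 0.5) = σ. With 50 per arm and 80% power the detectable difference is 0.566σ. Under ANCOVA it is 0.566 × √0.75 = 0.490σ. Equivalently, 50 per arm with ANCOVA matches 50/0.75 ≈ 67 per arm with change scores.

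**Chance imbalance.** The standard error of the baseline difference is √(2/50) = 0.2 SD, so an absolute imbalance above 0.2 SD occurs in about 32% of randomisations. Given an imbalance of 0.2 SD, the change-score estimate moves by (1 − ρ) × 0.2 against the arm that starts higher: 0.14σ at ρ = 0.3, 0.10σ at ρ = 0.5 and 0.04σ at ρ = 0.8.

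**Unequal SDs.** If the follow-up SD is k times the baseline SD, the ratio is k²(1 − ρ²)/(k² + 1 − 2ρk). At ρ = 0.7 and k = 1.3 this is 1.69 × 0.51/(1.69 + 1 − 1.82) = 0.862/0.870 ≈ 0.99, almost no gain. At ρ = 0.7 and k = 0.77 it is about 0.59, a larger gain than with equal SDs.

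**If follow-up scores are compared instead.** The variance ratio of ANCOVA to the unadjusted test is 1 − ρ²: 0.91 at ρ = 0.3, 0.75 at 0.5 and 0.36 at 0.8. A 0.2 SD imbalance then shifts the estimate by 0.2ρ in the other direction, in favour of the arm that starts higher.

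**The case against.** The strongest reply is that nothing here is invalid. A t test on change is a proper randomised comparison: it keeps its type I error, and its standard error already reflects chance imbalance. A reader might infer from the regression-to-the-mean argument that the planned primary result is biased. The document does not support that: the shift exists only conditionally on the imbalance that occurs, and it averages to zero over randomisations. At ρ = 0.5 the 0.10σ shift is half of one standard error (0.20σ). This stands, and it limits the point to efficiency and conditional bias.

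A second reply is that the t test sentence names neither FACT-B nor change, and that Table 1 does not say whether its entries are changes or follow-up scores. This stands as a limit on the figures, since the (1 + ρ)/2 ratio applies only to change scores. It does not remove the point, because a comparison of follow-up scores would be equally unadjusted.

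A third reply is that covariates are often left to an SAP that is not shown. Missing detail would indeed be no finding. Here, however, the protocol names a test, and the comment concerns that named choice.

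Finally, it is tempting to read 65% to 90% as the range of the gain for this trial, or to take six months as the endpoint time. Neither is supported. The range rests on equal SDs and an assumed ρ, and section 2.3 says only "The intervention duration ranges from hospitalization to 6 months postoperatively", which is a treatment period and not an assessment time.

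**Conclusion.** The point holds as a recommendation to use a better method, not as an error that invalidates the trial. The baseline score implied by the main outcome is not used as a covariate, and ANCOVA would generally estimate the same treatment difference more precisely while removing the conditional shift from baseline imbalance. The saving in variance is 35% to 10% for ρ from 0.3 to 0.8, given change scores and equal SDs. It may be larger or close to nothing if the SDs differ. That a baseline is collected is inferred from the word 'change', and that the t test applies to FACT-B is inferred from its being the only method that fits. Both inferences are strong, but the sponsor should confirm them.

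**What to change.** In section 2.5, state that FACT-B at the trial's primary assessment time will be analysed by ANCOVA with treatment group and baseline FACT-B as terms, reporting the adjusted mean difference with its 95% CI. Modelling the follow-up score or its change gives the same treatment estimate once baseline is in the model. Use the same model for each subscale with its own baseline, and for the NRS if a baseline is recorded. Keep the t test on change as a sensitivity analysis, and correct 'qualitative' to 'quantitative'. Name the assessment time in the same sentence, taking it from the trial's own schedule.

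Prespecify this before outcome data are compared, so that the adjustment cannot appear to have been chosen on the results. Provided the baseline is recorded as the endpoint implies, the cost is wording only: no extra patients or measurements, and the model runs in the SPSS version already named.

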## Results

3

Table 1 shows the clinical results between study group and control group.

**Table 1 T1:** Clinical results between study group and control group.

Variables	Study group (n = 50)	Control group (n = 50)	*P*
Physical well-being			
Social well-being			
Emotional well-being			
Functional well-being			
Breast cancer-specific subscale for additional concerns			
Numerical rating scale			
Postoperative complications			

## Discussion

4

Breast cancer is one of the most prevalent malignancy among female population all over the world.^[16]^ It ranks first in incidence rate and second in mortality. As a result, breast cancer still is a significant issue of public health. The improvement in screening and treatment modalities has made it possible to detect the disease at an early stage. The major treatment for the early breast cancer is surgery accompanied by the adjuvant therapies. Nevertheless, these treatments can lead to adverse reactions containing sleep disturbances, fatigue, and pain. Such effects can markedly worsen a patient's health-related quality of life, particularly during the periods immediately after surgery and adjuvant therapy.^[17]^ Some methods have been utilized for the improvement of the life quality for female breast cancer patients, containing physical activity, the training based on mindfulness, biopsychosocial intervention, as well as group-based intervention.^[18,19]^ Despite these programs have achieved satisfactory results, there is rarely a comprehensive method that involves social, psychological, and physical rehabilitation in postoperative period. With the popularity and wide coverage of mobile Internet access, WeChat, a kind of free communication software based on mobile Internet, has become one of the most widely used social media. Considering that it is not limited via geographical location and time, the multi-mode nursing plan based on WeChat may have significant benefits for patients. Although WeChat can help improve the quality of nursing, the multi-mode nursing project of early rehabilitation of breast cancer patients based on WeChat has not been reported.

## Conclusion

5

This paper has guided nurses to develop an evidence-based protocol to improve patient care for postoperative women with breast cancer.
